## Abstract

**Background:**

Frailty is a common and clinically significant condition in older adults, predominantly due to its association with adverse health outcomes such as hospitalisation, disability and mortality. Exercise interventions have been shown to be a beneficial treatment for frailty. However, more high-quality studies are needed to assess the feasibility and impact of these interventions in frail geriatric populations within different settings, and their impact on broader aspects of health and well-being.

**Methods and analysis:**

This study will use a 2-week, interventional, independent measures research design in order to assess the feasibility and impact of two specially adapted exercise training interventions (a specially adapted resistance training intervention, and Move It Or Lose It: an established community-based exercise intervention for older adults) aimed at improving the multidimensional health and functional capacity of frail geriatric hospital inpatients.

**Ethics and dissemination:**

This study has received a favourable ethical opinion by the Coventry and Warwickshire NHS Research Ethics Committee and sponsorship by the University of Birmingham after review by the sponsors research governance office. The findings will be disseminated through publication in open access scientific journals, public engagement events, online via social media, conference presentations and directly to study participants on request.

**Trial registration number:**

NCT03141866

Strengths and limitations of this studyMixed-methods feasibility study employing both quantitative and qualitative research methodologies.Specially adapted exercise interventions for frail geriatric populations.Difficult to reach (and often excluded) participant population.Single-site study.

## Background

Frailty is a common and clinically significant condition within geriatric populations,^1^ predominantly due to its association with adverse health outcomes such as hospitalisation, disability and mortality.^1–6^ Although the exact prevalence of frailty within this population is poorly defined due to the lack of a single standardised operational definition for the classification of frailty, it is generally believed that the prevalence of frailty among community-dwelling older adults ranges between 7.0% and 16.3%.^1 7^ Presently, there are no well-evidenced, pooled estimates of the overall prevalence of frailty within geriatric hospital inpatients. However, there are several studies which have primarily aimed to produce estimates of the prevalence of frailty within this population.^8–15^ Although there is an evident need for more robust research to thoroughly assess the overall prevalence of frailty within this setting, through analysis of these existing studies, dependent on the criteria utilised, the prevalence of frailty in geriatric hospital inpatients ranges from ~27% to 94%. In the five of the eight studies which utilised the Fried Frailty phenotype^2^ as the operational definition of frailty, there is a narrower range (27%–48.5%), with a mean prevalence of frailty across the five studies of 37.5%±6.76%.^8 9 11 12 16^

Although there is no one standardised and universally utilised operational definition of frailty, one of the most commonly utilised is the Fried frailty phenotype.^2^ This proposes that frailty be defined as a clinical syndrome in which three or more of the five following criteria are present: unintentional weight loss (≥10 lbs in the last year), self-reported exhaustion, weakness (grip strength), slow walking speed and low levels of physical activity.

Exercise interventions have been proposed as potentially offering the best form of treatment for frail older adults^17^; with exercise shown to be a significantly beneficial treatment for this population with regard to multiple components of health, and even shown to mediate the reversal of frailty in some cases.^18–21^ However, while there is evidence of the benefits of exercise relating to the prevention, treatment and reversal of frailty, it is universally noted that there needs to be more high quality studies within this area to truly assess the impact of exercise in frail geriatric populations within different settings, particularly relating to its effects on broader aspects of health and well-being.^1^

This present study will assess the feasibility and efficacy of short duration (2 weeks), intensive (5 days/week), specially adapted exercise interventions within a delayed transfer of care hospital ward setting. Feasibility will relate to the eight main areas of focus for feasibility studies,^22^ while efficacy will be assessed through limited efficacy testing of the impact of the interventions on the secondary dependent variables relating to multidimensional health and functional capacity.

Such research is very timely and pertinent, as current demographic trends indicate that by the year 2030 almost one in six of the European population will be aged 60 years or over, and the number of older people will grow to 247 million by 2050, representing a 35% increase from 2017, with one in four older adults being over 85 years by 2040.^23^ This coupled with continual progressive declines in the rate of physical activity, at all stages of the lifespan,^24^ leaves the population particularly susceptible to the development of disease and comorbidities associated with a lack of physical activity and an increase in sedentary behaviour.^25^ Moreover, acute hospital admission for older adults are associated with further loss of physical activity and represent a period of increased susceptibility to sarcopenia and frailty.^26^ Frailty is associated with longer stay and increased rates of mortality in hospitalised older adults, as well as serving as a predictor of readmission.^12 27^ Therefore, there is an urgent need to examine the effect of such interventions within this setting, and whether these interventions can be employed to improve various aspects of health in frail older populations in inpatient hospital ward settings, as well as their efficacy in specifically treating, preventing and reversing frailty. Preliminary research has shown some success in the implementation of exercise interventions to reverse functional decline in general geriatric inpatient populations^28^; however, to the authors’ knowledge, this present study is the first to attempt such an intervention in frail delayed transfer of care patients.

## Methods and analysis

### Aims and objectives

The primary aim of this study is to assess the feasibility of a proposed future trial in this setting, which aims to assess the impact of specially adapted exercise interventions on the physiological, psychological, cognitive, social and emotional health, and functional capacity of frail geriatric populations within a hospital ward setting; recognising health as a multifactorial concept incorporating multiple inter-related dimensions. The secondary aim of this feasibility study is to assess the potential efficacy of the interventions on the primary dependent variables of the proposed future clinical trial within this setting.

The primary and secondary aims of this study will be achieved through the sequential achievement of the following objectives: (1) recruitment of eligible participants from the Harborne Ward of the Queen Elizabeth Hospital Birmingham, [name], United Kingdom (UK); (2) baseline assessment of the secondary dependent variables related to multidimensional health; (3) assessment of the feasibility of the study as it relates to the eight-primary areas of focus for feasibility studies (acceptability, demand, implementation, practicality, adaptation, integration, expansion and limited-efficacy testing)^22^; (4) post-intervention assessment of all primary and secondary dependent variables.

The research questions of this study relate to the eight aforementioned areas of focus of this feasibility study, incorporating the following questions relating to the feasibility and efficacy of the study within this setting: Can it work? Will it work? Does it work?^22^ (table 1).

**Table 1 T1:** The eight primary areas of focus, outlining the research questions and methods of assessment

Area of focus	Potential questions	Methods of assessment
Acceptability	Will the proposed population be interested in participating in the study? What will the uptake be? Will the programme be judged as suitable by the delivers of the programme in addition to the programme participants? Participant’s opinions on hypothetically being randomised into a control group during a proposed future clinical trial?*	Participant uptake analysis (All participants approached and eligible for the study, all of those successfully recruited to the study). Semi-structured interviews with participants. Focus groups with study support staff.
Demand	Will the proposed population of hospital inpatients participate in the study? What will adherence rates be? Are the staff on the ward open to the idea of having exercise interventions potentially on the ward long term if it proves effective?	Analysis of uptake rates. Exercise intervention adherence rates. Focus groups with study support staff/ward staff.
Implementation	What are the possible logistical issues with the setting which will need to be addressed or accounted for prior to the clinical trial? Can the interventions be successfully carried out within this setting? Can a single or double bind be successfully implemented within this setting?	Semi-structured interviews with study participants. More in-depth with focus groups with study support staff.
Practicality	What are the practical implications of the study with relation to time commitment of the researchers, relating to both the implementation of the interventions, and the testing of participants for the dependent variables of the proposed future clinical trial? Is it viable to potentially conduct follow-up testing on participants in the proposed future clinical trial? Do any alterations need to be made to the proposed primary dependent variables of the future clinical trial? If the interventions are successful in influencing parameters of health and functional capacity, will it potentially be possible to assess if these improvements are sustained during a 2-week follow-up in the proposed future clinical trial, if the same is found?	Semi-structured interviews with study participants. Focus groups with support staff.
Integration	How will the ward staff appraise the study? Will the interventions be easily integrated into the existing culture, protocols and procedures within the ward seamlessly?	Focus groups with ward/support staff.
Adaptation	Will any further adaptations be required to the existing interventions to make them more feasible or appropriate within this setting?	Semi-structured interviews with participants.
Expansion	Can the Move It or Lose It intervention (an established chair-based exercise programme for older adults) be successfully expanded to this setting? Can be specially adapted resistance training equipment be successfully expanded to this setting?	Semi-structured interviews / focus group with the ward/study support staff.
Limited-efficacy testing	Is 2 weeks a sufficient duration to potentially provide significant benefit to patients? Can intensive (5–6 days/week), short duration (2 weeks) physical activity interventions improve markers of multidimensional health, in very frail individuals?	Analysis of the secondary dependent variables within the study (primary dependant variables of the future clinical trial). Analysis of uptake and adherence rates. Analysis of the level of satisfaction with the interventions through questionnaires with participants post-intervention.

*Participants within the feasibility study will not be recruited as participants within the proposed future clinical trial in order to protect the scientific validity of the proposed future clinical trial, as the participants within the feasibility study will already have undergone the interventions, or similar interventions. However, participants within the feasibility study will likely not still be residents on the ward, as the average stay for participants on the ward is ~3.5 weeks. As such once the proposed future clinical trial has commenced, all participants within the feasibility trial will likely have left the ward well in advance.

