### Eligibility

This study is open to both men and woman whom meet the following eligibility criteria: inpatient on the Harborne ward of the Queen Elizabeth hospital Birmingham, [name], UK; ≥65 years of age; frail according to the Fried Frailty Phenotype criteria^2^; ability to speak and read in English; not currently taking part in any other clinical trial which could potentially impact on or influence the findings of this study; not currently terminally ill with life expectancy less than the duration of the study; no severe sensory impairment which would profoundly impact on ability to undergo the intervention, even once appropriate adaptations have been made; anticipated by their care team to remain on the ward for ~21 days post-enrolment into the study.

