### Dependent variables

#### Primary dependent variables

The primary dependent variables will relate to the eight primary areas of focus of feasibility studies^22^ (utilised to establish the feasibility of a proposed future clinical trial within this setting), relating to: acceptability, demand, implementation, practicality, adaptation, integration, expansion and limited-efficacy testing.

These dependent variables will be assessed through semi-structured interviews with study participants and focus groups with ward staff post-intervention. Participant uptake and adherence records will also be employed throughout. These methods seek to attain answers to the following questions and parameters relating to the eight primary areas of enquiry for this feasibility study outlined in further detail in table 1.

In order to enhance trustworthiness in the qualitative component of this research, several methods will be employed:

The researcher gathering the data will keep a reflective journal in which they will record information about themselves, their activities and the methods used. Field notes will include time, date and location, participant’s actual notes, and the researcher’s own questions and comments. This will lend to logging and documenting what is learnt about the study, the intervention, the setting, the participants, and used to refine focus for future interviews through assessing the following questions: What is important? What is it I need to find out more about? What would I want to focus on more closely if I could do the interview again, or in future interviews?^31^

Data will be gathered from study participants and ward staff in order to collect data from multiple sources (triangulate information). This study will also employ more than one researcher to analyse the qualitative data in order to enhance triangulation and validity.

Enough details will be given about the participants and the setting to make decisions about the quality of the findings from the qualitative analysis. Detailed descriptions about the participants experiences and the setting will be provided by the researcher.

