### Identification, consent and recruitment

#### Identification

Patients on the ward at the commencement of the study will initially be screened by their care team for the known presence of any severe sensory impairments which would exclude them from participation. Due to the study’s rolling recruitment, this initial screening will continue throughout the study as additional patients are admitted to the ward. Participant information sheets will not be distributed to patients who are deemed to be medically unfit or due for imminent discharge as identified by their care team. All other aspects of the screening process will occur after consent has been obtained. After identification, potential participants will be approached by the researcher with an information sheet related to the study and asked if they would be interested in participating, or if they would like to receive more information about the study (online supplementary file 2). The information sheet will contain all the most pertinent information relating to the study and specifically what it would require from potential participants. Potential participants will be given ≥24 hours to consider whether or not they would like to participate.

10.1136/bmjopen-2019-031159.supp2Supplementary data

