#### Recruitment

Following consent being obtained from the participant themselves, or the obtainment of a declaration from a consultee, all consented participants will be screened for the remaining eligibility criteria.

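### Uptake is set on patients who were approached and eligible, but frailty is checked only after consent, so that denominator cannot be observed for patients who decline

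*Protocol article*

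**What the plan says.** In Aims and objectives, Table 1 gives the Acceptability row this method: "Participant uptake analysis (All participants approached and eligible for the study, all of those successfully recruited to the study". The same row asks what the uptake will be. The Demand row reuses the measure ("Analysis of uptake rates. Exercise intervention adherence rates"), and the Limited-efficacy row also lists uptake. Under Primary dependent variables, "Participant uptake and adherence records will also be employed throughout".

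The order of screening is set elsewhere. Under Identification, patients will "initially be screened by their care team for the known presence of any severe sensory impairments which would exclude them from participation", and "Participant information sheets will not be distributed to patients who are deemed to be medically unfit or due for imminent discharge". The same section then states: "All other aspects of the screening process will occur after consent has been obtained". Recruitment repeats that, once consent or a consultee declaration is in hand, "all consented participants will be screened for the remaining eligibility criteria". Eligibility requires patients to be "frail according to the Fried Frailty Phenotype criteria". By the definition in the Background, that status depends partly on grip strength, walking speed and self-reported exhaustion.

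**The concern.** The uptake measure needs to know which approached patients were eligible. The screening order produces that knowledge only for patients who have already consented. Those who decline determine how far uptake falls below 100%, and their frailty is never assessed.

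Two outcomes follow if Table 1 is applied with the full eligibility list. Either the denominator cannot be formed, or it shrinks to patients known to be eligible. All of those have consented, and the ratio then says nothing about willingness to take part. Another team could divide by everyone approached and get a much lower figure from the same ward data, under the same label. A primary feasibility measure should not depend on which of these is chosen after the counts are seen.

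**Working it through.** The protocol states no uptake figure, so there is none to reproduce. The check is whether the stated rate can be computed from what is observed.

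**Step 1. What is known, and when.**
- Before the approach: ward residence and age (from records), known severe sensory impairment, medical unfitness, imminent discharge.
- After consent only: Fried status and the other remaining criteria. The Eligibility section also asks for an anticipated stay of about 21 days, which is stricter than not being due for imminent discharge.
- Never, for a patient who declines: Fried status.

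**Step 2. The rates in symbols.** Let A be the number approached, f the proportion of them who are Fried-frail, and c the probability of consent, taken first as equal in frail and non-frail patients. Treat frailty as the deciding criterion, and suppose that all frail consenters are enrolled.
- Intended rate, recruited / (approached and eligible) = A·f·c / (A·f) = c. It needs A·f, which is not observed.
- Recruited / known eligible = A·f·c / (A·f·c) = 100%.
- Consented / approached = c.
- Eligible / consented = f.
- Enrolled / approached = f·c.

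**Step 3. Numbers.** The Background gives f = 27% to 48.5%, mean 37.5%, from five inpatient studies that used the Fried phenotype. Assume A = 100 and c = 50%; neither is in the protocol.

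| f | Enrolled | Recruited / known eligible | Consented / approached | Enrolled / approached | Highest ÷ lowest |
|---|---|---|---|---|---|
| 27% | 100 × 0.5 × 0.27 = 13.5 | 100% | 50% | 13.5% | 100/13.5 = 7.4 |
| 37.5% | 100 × 0.5 × 0.375 = 18.75 | 100% | 50% | 18.75% | 100/18.75 = 5.3 |
| 48.5% | 100 × 0.5 × 0.485 = 24.25 | 100% | 50% | 24.25% | 100/24.25 = 4.1 |

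If c is varied from 30% to 70%, enrolled / approached runs from 0.27 × 0.30 = 8.1% to 0.485 × 0.70 = about 34%.

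**Step 4. What can be said about the intended rate.** Let R be the number recruited and D the number who decline with frailty unknown. If every decliner is eligible, the rate is R/(R+D). If none is, it is 100%. With R = 30 (the target sample) and assumed values of D:
- D = 20: 30/50 = 60%, so 60% to 100%.
- D = 50: 30/80 = 37.5%, so 37.5% to 100%.
- D = 100: 30/130 = 23.1%, so 23.1% to 100%.

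**Step 5. Does consented / approached recover it?** Only if willingness is unrelated to frailty. Suppose 40% of frail and 60% of non-frail patients consent, with f = 37.5%. Then consented / approached = 0.375 × 0.40 + 0.625 × 0.60 = 0.15 + 0.375 = 52.5%, while uptake among frail patients is 40%.

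**The case against.** The best defence is that Table 1 names two groups to be counted and states no formula. If eligible is read as having passed the care team's pre-screen, the rate can be computed. If recruited is read as consented, which the order of words in Table 2 allows, the rate is willingness among those approached. No text tells the team to drop decliners. This is also a condensed article whose participant-flow figure is not shown, and the raw counts could still be reported.

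Part of this stands: the fault is a definition that does not fit the screening order, not an instruction to report 100%. But the article does not give the pre-screen reading, and its Eligibility section includes frailty. Under that reading, with recruited meaning enrolled, the rate would mix refusals with post-consent screen failures. A fuller document could choose another definition, but it could not supply frailty data on decliners that the stated sequence does not collect.

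Some stronger inferences are tempting and not supported:
- That all eligibility is assessed after consent. Three filters come before the approach, and age and ward status are on record.
- That Acceptability and Demand rest on uptake alone. Interviews, focus groups and adherence also feed them, and Statistical methods brings uptake in as additional information alongside the qualitative analysis.
- That the future trial's recruitment rate will be projected from this figure. That would be a natural use, but the article does not state it.

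The size is also illustrative. The Background quotes up to about 94% frailty under other criteria. If prevalence on this ward were that high, yield at 50% consent would be 0.94 × 50% = 47%, close to willingness. The ratio among known eligible patients would still be 100%.

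**Conclusion.** The point holds, with moderate severity. The Table 1 denominator and the screening order in Identification and Recruitment do not fit together: eligibility of decliners is largely unknown, so uptake among eligible patients is not identified. Limited to patients known to be eligible, the rate is close to 100% by construction, apart from any lost between confirmed eligibility and enrolment.

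The four- to seven-fold spread rests on an assumed 50% consent and on prevalence from other inpatient studies. It compares different quantities, so it shows how much the choice of denominator matters and is not an estimate of bias. The conflict itself needs neither assumption. Severity stops at moderate because uptake is one of several inputs and no progression threshold or hypothesis depends on it.

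**What to change.** Replace the uptake entry in Table 1 with the counts at each observable step and these rates, each with a 95% CI:
1. Approached / ward patients pre-screened by the care team.
2. Consented (by the patient or through a consultee) / approached, labelled as willingness among those approached, not among frail patients.
3. Eligible / consented.
4. Enrolled / approached, labelled as recruitment yield.

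State that uptake among eligible patients is not identified because decliners' frailty is unknown, or report its bounds, from R/(R+D) to 100%. Let the Demand and Limited-efficacy rows refer to the same rates.

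The cost is a wording change and keeping a count at every step. The article mentions uptake records but not a screening log, so the team should confirm that these counts are kept. No new patient assessment is needed. The headline uptake figure will look less favourable.
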